### Sample size calculation

2.13

The sample size is estimated by assuming a 50% improvement rate at the end of 8 weeks in the active group and a 15% in the sham group, which were based on our pilot trial of the effect of tACS in adults with major depression disorder.^[38]^ Thus, each group will be recommended to have a minimum sample size of 26 with a power to 80% and a 2-tailed α level of 5%.^[53]^ Considering the 20% attrition rate, 32 evaluable participants will be required for each group. And the total sample size will be 70.

### Statistical analysis

2.14

All data from the study will be analyzed by an independent biostatistician using SAS statistical software, version 9.4 (SAS Institute Inc) and will be considered statistically significant at a *P* value < .05, and all tests are two-sided. Outcomes are based on the intention-to-treat analysis. Missing data will be monitored using the multiple imputation method. Continuous variables will be summarized as mean and standard deviation (SD). Categorical variables will be described as frequency and percentage. Between-group comparisons will be tested by the Mann-Whitney *U* test for continuous variables and the Chi-square test for categorical variables.

The primary outcome will compare the proportion of participants achieving an improvement of depression per HAMD-17 between the 2 groups after 8 weeks of the trial. Secondary outcome analyses will be conducted based on standard statistical principles for comparison of parametric or non-parametric distributions as appropriate. Logistical regression analyses will be utilized to analyze the primary and secondary variables between groups, such as HAMD-17 total score, NIHSS score, mRS score, BI score, CGI-I score, CGI-S score, and epileptic seizure. The secondary outcomes on changes of HAMA, MMSE, MoCA, RBANS, and beta-and gamma-oscillations will be analyzed using mixed-effects models, controlling for time of measurement.

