#### Primary outcomes

2.6.1

The primary outcome is the proportion of participants having an improvement at week 8, which includes the response per HAMD-17 defined as a ≥ 50% reduction from the baseline^[41]^ or clinical recovery (score ≤ 7).^[21]^

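### The analysis section names the HAMD-17 total score, not the binary week-8 improvement, as a logistic-regression variable, and does not say whether logistic regression or chi-square decides the primary comparison

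*Protocol article*

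**What the plan says.** All of this is in the protocol article.

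- **Primary outcomes (2.6.1)** defines a binary endpoint at week 8: "a ≥ 50% reduction from the baseline" in HAMD-17, or clinical recovery (score of 7 or less).
- **Statistical analysis (2.14), general rule:** between-group comparisons use Mann-Whitney for continuous variables and "the Chi-square test for categorical variables".
- **Statistical analysis (2.14), primary comparison:** "The primary outcome will compare the proportion of participants achieving an improvement of depression per HAMD-17 between the 2 groups". This sentence names no test.
- **Statistical analysis (2.14), model:** "Logistical regression analyses will be utilized to analyze the primary and secondary variables between groups, such as HAMD-17 total score, NIHSS score, mRS score". The list continues with BI, CGI-I, CGI-S and epileptic seizure.
- **Adverse effects (2.7)** defines seizure as a proportion of participants. **Inclusion and exclusion criteria (2.3)** excludes a history of seizures. No expected seizure rate is given.
- **Abstract (Methods)** mentions logistic regression and mixed-effects models, and no chi-square test.

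**The concern.** There are three issues, all in what the text states.

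1. **The response variable is misnamed.** The sentence that assigns a model to the primary variable names a multi-point total score, whereas 2.6.1 defines a yes/no endpoint. Taken literally, the model is applied to a variable that is not the primary outcome. Taken as shorthand, the endpoint is mislabelled where it should be clearest.

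2. **Two methods cover one proportion.** The chi-square rule and the logistic sentence both reach the primary outcome, and significance is set at P < .05 without saying whose P value counts. A result close to 0.05 could then be called either way.

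3. **Sparse seizure data.** With prior seizures excluded and 70 participants, an arm with no seizure is likely. Ordinary maximum-likelihood logistic regression then has no finite odds ratio to report.

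**Working it through.** **Inputs.** Rates come from Sample size calculation (2.13): "assuming a 50% improvement rate at the end of 8 weeks in the active group and a 15% in the sham group". Error rates: "a power to 80% and a 2-tailed α level of 5" percent. The total is 70 at 1:1, so 35 per arm. Seizure risks are assumptions.

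**Step 1. Reproduce the plan's figure.** The plan gives 26 per group.

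- Pooled-variance formula, with mean rate (0.50 + 0.15)/2 = 0.325:
  n = [1.960·√(2·0.325·0.675) + 0.842·√(0.50·0.50 + 0.15·0.85)]² / 0.35² = 26.9, so 27.
- Arcsine formula: n = 2·(1.960 + 0.842)² / 0.775² = 26.1.

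The 26 is reproduced closely enough. The sample size is not in question here.

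**Step 2. Compare the two named methods.** All 2×2 tables with 35 per arm were enumerated with binomial probabilities. Each was tested at 0.05 by the uncorrected Pearson chi-square and by the Wald test of an unadjusted logistic model. A table with an empty cell counts as non-significant for Wald.

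| True rates | Pearson rejects | Wald rejects | Verdicts differ |
|---|---|---|---|
| 50% vs 15% | 90.3% | 89.4% | 0.9% |
| 15% vs 15% | 5.3% | 2.6% | 2.7% |
| 30% vs 30% | 5.1% | 4.8% | 0.3% |

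At 35 per arm, Wald never rejects where Pearson does not. Choosing the smaller of these two P values therefore has the same error rate as Pearson alone.

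**Step 3. An example near the threshold.** Take 8 of 35 vs 2 of 35 responders.

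- Pearson: expected counts are 5 and 30 in each arm, so X² = 2·(3²/5) + 2·(3²/30) = 4.2 and p = 0.040.
- Wald: log odds ratio = ln[(8·33)/(2·27)] = 1.587; SE = √(1/8 + 1/27 + 1/2 + 1/33) = 0.832; z = 1.907 and p = 0.056.

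The same data give opposite verdicts at 0.05.

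**Step 4. Baseline adjustment.** Power of the unadjusted and the baseline-adjusted logistic model was simulated (35 per arm, 2,000 trials per setting, likelihood-ratio test) for assumed log odds ratios per SD of the covariate:

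| Log OR per SD | Unadjusted | Adjusted |
|---|---|---|
| 0 | 90.6% | 89.9% |
| 0.5 | 91.1% | 91.4% |
| 1.0 | 90.3% | 94.2% |

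The article does not state how prognostic baseline HAMD-17 is, so the gain may be nil or moderate.

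**Step 5. Seizures.** With risk p in both arms and q = (1 − p)^35, the chance that at least one arm has no event is 1 − (1 − q)².

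| Assumed risk | q | Expected events in 70 | P(an arm has none) |
|---|---|---|---|
| 1% | 0.703 | 0.7 | 91% |
| 2% | 0.493 | 1.4 | 74% |
| 5% | 0.166 | 3.5 | 30% |

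**The case against.** The best defence is that the text can be read sensibly. The Abstract names only logistic regression and mixed models. The chi-square sentence follows the descriptive summaries and names no outcome. The logistic list names instruments, and Secondary outcomes (2.6.2) turns NIHSS, mRS, BI and CGI into proportions, so the HAMD-17 entry is probably shorthand for the 2.6.1 endpoint. Logistic regression can also be ordinal. This carries weight: it makes the point a correction of wording, not evidence of a wrong design. But 2.14 never limits the chi-square rule to descriptive use, and the total score is still not the primary outcome on any reading.

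Four stronger readings are tempting and are not supported:

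- **The choice of test costs much power.** A large gap appears only between continuity-corrected and uncorrected chi-square, and the article mentions no correction. The two methods it names differ by 0.9 points at 35 per arm.
- **Omitting baseline HAMD-17 is an error.** An article may leave covariates to the full protocol or SAP, and the unadjusted comparison is valid under randomisation. Adjustment is a recommendation.
- **The HAMD-17 score has no valid analysis.** The continuous score is not a listed outcome, so none is owed. The Mann-Whitney rule would cover it. A power figure for it would need an assumed distribution.
- **Logistic regression does not fit seizures.** Seizure is binary, so the model suits its type. The difficulty is sparse data only.

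**Conclusion.** The point holds as a correction to section 2.14. The variable named for logistic regression does not match the binary primary outcome in 2.6.1, and the deciding test is not identified among two that apply. The effect on the trial's operating characteristics is small: 0.9% of trials change verdict under the planned rates and 2.7% under 15% in both arms. It matters only when the result lies close to 0.05. These figures assume 35 analysed per arm, the uncorrected Pearson test and an unadjusted Wald test.

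The seizure point is practical and depends on assumed risks. At 1% to 2% an empty arm is the likely outcome; at 5% it happens in about three trials of ten.

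**What to change.** Reword section 2.14 as follows.

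1. State that the primary analysis is logistic regression of week-8 HAMD-17 improvement (yes/no, as in 2.6.1) on arm and baseline HAMD-17, reported with a risk difference and its 95% CI. State the test that gives the primary P value.
2. Make the unadjusted chi-square test of the same proportion a sensitivity analysis, and say whether it is continuity-corrected.
3. In the logistic list, replace the HAMD-17 total score with the binary improvement endpoint.
4. Report seizures as counts per arm with exact confidence intervals in place of a logistic odds ratio.

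The cost is a few sentences, settled before unblinding. Baseline HAMD-17 is already measured for eligibility, so no new data are needed, and the sample size stays as it is.

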### Study design

2.1

This is an 8-week, randomized controlled trial (RCT) aimed to evaluate the efficacy of tACS in treating PSD. Seventy participants with PSD will be recruited from the Department of Neurology, Xuanwu Hospital of Capital Medical University, Beijing, China. After obtaining written informed consent from participants, potential participants will be screened for their eligibility. If eligible, they will be randomized to either the active or sham intervention group with a ratio of 1:1. Participants will undergo a 4-week intervention period (week 4), and another 4-week observational follow up (week 8). Outcomes will be evaluated for all participants at 3 time points: at baseline, at week 4, and week 8. All procedures of this trial will follow the strictly Consolidated Standards of Reporting Trials (CONSORT) guidelines (see Fig. 1) and Standard Protocol Items: Recommendations for Interventional Trials (SPIRIT) Checklist.

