#### Secondary outcomes

2.6.2

The proportions of participants achieve an improvement in neurological function at weeks 4 and 8 during the trial. The improvement will be decided by a reduction of ≥ 50% or the total score of 0–1 in the National Institute of Health Stroke Scale (NIHSS) score (ranging from 0 to 42, higher scores indicate a more severe neurological deficit).^[42]^

The proportions of participants achieve an improvement in independence at weeks 4 and 8, as measured by a modified Rankin Scale (mRS) over the trial (scores on this scale range from 0 to 6, with higher scores indicating more significant disability),^[43]^ and the improvement is defined as 0, 1, and 2 in mRS.

The proportions of participants with a Barthel Index (BI) score of ≥90 at weeks 4 and 8 during the study. The BI is used to assess the activities of daily living (ranging from 0 to 100, higher scores indicate increased independence).^[44]^

The proportions of participants have improvements in the Clinical Global Impression scale (CGI). The CGI includes the severity scale (CGI-S) and the improvement scale (CGI-I), both are 7-point rated scales, with lower scores indicating less illness and more improvement, respectively.^[45]^

The changes of participants on anxiety symptoms at weeks 4 and 8 assessed by the Hamilton Anxiety Rating Scale (HAMA), and it ranges from 0 to 56, and higher scores indicate more anxiety.^[46]^

The changes of participants on cognitive function at weeks 4 and 8, as evaluated by the Mini-Mental State Examination (MMSE) (range from 0 to 30, higher scores indicate impaired cognition)^[47]^ and the Montreal Cognitive Assessment (MoCA) (ranging from 0 to 30, and higher scores indicate impaired cognition in different cognitive domains).^[48]^

The changes of beta-and gamma-oscillations at weeks 4 and 8, as assessed via resting-state high-density electroencephalogram (rsHEEG) by utilizing a 128 channel electroencephalogram (EEG) system (Geodesic EEG system 400, Electrical Geodesics, Inc., OR) at baseline, week 4, and week 8. Gamma and beta-oscillations induced by tACS correlate with aspects of executive function and emotional regulation.^[49,50]^

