The variations of cognitive status at weeks 4 and 8, as measured by the repeatable battery for the assessment of neuropsychological status (RBANS), which includes different domains of attention, immediate and delayed memory, language, and visuospatial/constructional. And the Chinese version of RBANS has been certified as a reliable tool for cognitive function assessment with reasonable reliability and validity.^[51]^ The higher scores indicate the better in the neurocognitive state.

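### As written, the mixed models for HAMA, MMSE, MoCA, RBANS and EEG pool weeks 4 and 8 and do not adjust for baseline; separate visit contrasts with a baseline covariate would be a free improvement

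*Protocol article*

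**What the plan says.** The model is given in one sentence of section 2.14 (Statistical analysis), which says that the changes in HAMA, MMSE, MoCA, RBANS and beta/gamma oscillations "will be analyzed using mixed-effects models, controlling for time of measurement". It names no other term. Treatment arm is not listed either, although a between-group comparison must contain it.

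Section 2.6.2 (Secondary outcomes) defines the outcomes by week: "The changes of participants on anxiety symptoms at weeks 4 and 8" for HAMA, "The changes of participants on cognitive function at weeks 4 and 8" for MMSE and MoCA, "The changes of beta-and gamma-oscillations at weeks 4 and 8" for EEG, and "The variations of cognitive status at weeks 4 and 8" for RBANS.

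Baseline is available. Section 2.1 (Study design) says: "Outcomes will be evaluated for all participants at 3 time points: at baseline, at week 4, and week 8". By sections 2.1 and 2.5, stimulation runs for the first four weeks and the next four weeks are observation only.

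The preceding paragraph of section 2.14 also gives a general rule that between-group comparisons of continuous variables use the Mann-Whitney test. It does not say whether that rule extends to the outcomes assigned to mixed models.

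**The concern.** Weeks 4 and 8 ask different questions. Week 4 measures the effect at the end of treatment, and week 8 measures what is left four weeks later. Controlling for a variable ordinarily means entering it as an additive adjustment. With arm and time additive, there is a single arm coefficient, assumed equal at both visits. That does not deliver the week-specific effects that section 2.6.2 sets out, and it cannot show whether an effect persists.

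The second issue is efficiency. A change score uses the baseline by subtracting it with a fixed weight of one. Entering baseline as a covariate lets the data set the weight and gives a narrower interval from data already collected. In a trial of 70 participants that gain is worth having.

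Third, the general Mann-Whitney sentence could be taken as a second, unadjusted test of the same outcomes. This is a minor ambiguity, but it leaves open which P value counts.

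**Working it through.** **Figures in the plan.** The article gives no effect size, SD, correlation or power for these outcomes, so there is nothing of its own to reproduce. Its one computed figure, 26 per group in section 2.13, concerns the binary primary outcome and plays no part here.

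**Inputs.**
- n = 28 per arm. Assumed, but consistent with section 2.13: 70 randomised 1:1 gives 35 per arm, and 20% attrition leaves 35 × 0.8 = 28.
- Effect d = 0.7 SD. Assumed.
- Correlation rho between any two visits = 0.5 to 0.7, with SD 1 at every visit. Assumed.
- Two-sided 5% level (section 2.14). Power = Φ(effect/SE − 1.96), with SE = √(V × 2/n) and V the variance per participant.

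**Step 1: what a pooled arm effect reports.** With change scores at weeks 4 and 8 as responses, additive arm and time terms and complete data, the arm coefficient is the mean of the two visit effects, (e4 + e8)/2.
- Effects 0.7 and 0.7 give 0.70.
- Effects 0.7 and 0.3 give 0.50.
- Effects 0.3 and 0.7 also give 0.50. Fading and growing effects cannot be told apart.
- Effects 0.7 and 0 give 0.35.

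**Step 2: power of the pooled effect when the effect is constant.** V = (1 + rho)/2 + 1 − 2rho = 1.5 − 1.5rho.
- rho 0.5: V = 0.75, power 86%.
- rho 0.6: V = 0.60, power 92%.
- rho 0.7: V = 0.45, power 97%.

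So with a constant effect, pooling change scores neither dilutes the estimate nor costs power. What is lost is the separation of the two visits.

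**Step 3: baseline adjustment at a single visit.** For a week-8 change score, V = 2(1 − rho). With baseline as a covariate, V = 1 − rho². The ratio is (1 − rho²)/[2(1 − rho)] = (1 + rho)/2.

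| rho | V, change score | V, baseline-adjusted | Ratio | Power, change score | Power, adjusted |
|---|---|---|---|---|---|
| 0.5 | 1.00 | 0.75 | 0.75 | 75% | 86% |
| 0.6 | 0.80 | 0.64 | 0.80 | 83% | 91% |
| 0.7 | 0.60 | 0.51 | 0.85 | 92% | 96% |

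For example, at rho 0.5 the change-score SE is √(1.00 × 2/28) = 0.267, and 0.7/0.267 = 2.62 gives 75%. The adjusted SE is √(0.75 × 2/28) = 0.231, and 0.7/0.231 = 3.02 gives 86%.

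**Step 4: the branch that the text does not describe.** If raw scores at all three visits were responses, with no arm-by-visit term, the arm effect would be (0 + e4 + e8)/3. That is 2/3 of a constant effect, or 1/3 of a week-4 effect that has gone by week 8. With V = (1 + 2rho)/3, power for a constant 0.7 would be 57%, 53% and 50% at rho 0.5, 0.6 and 0.7. These figures need baseline to be a response, whereas section 2.14 speaks of changes.

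**The case against.** The strongest reply is that the sentence is a summary. It does not say that time is the only term, it does not exclude an arm-by-visit term, and it omits even the arm. A mixed model with time as a factor is compatible with contrasts at weeks 4 and 8, and section 2.6.2 points that way. Interaction terms, covariance structure and baseline covariates are commonly left to a full protocol or SAP, which is not shown. This largely stands. It rules out saying that the planned models cannot estimate the week-specific effects, and nothing is claimed here about covariance structure. What remains is that the one role the text does give to time is that of a control variable, which fits poorly with outcomes defined at two separate weeks.

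Two stronger readings are tempting. A reader might infer that the baseline value is ignored. The documents do not support that: the outcomes are changes, so baseline enters by subtraction, and the comparison is unbiased under randomisation. A reader might also infer that the treatment effect is diluted to two thirds or one third, with power near 50%–57%. That needs baseline to be one of the modelled responses with no interaction, which the text does not say. On the literal change-score reading, a constant effect is estimated in full.

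On the Mann-Whitney test, the general sentence comes in the preceding paragraph, straight after the descriptive summaries, and the method for the named outcomes follows it. Taking the specific rule to govern is reasonable, so this is an ambiguity and not a stated second test.

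**Conclusion.** The point holds in limited form. As written, the model yields an arm effect pooled over the end of treatment and the end of follow-up, and it names no baseline covariate. Pooling matters when the two visits differ: 0.7 SD at week 4 and none at week 8 would be reported as 0.35 SD. Leaving baseline out as a covariate costs precision without causing bias. Adjustment reduces the single-visit variance to 0.75–0.85 of its change-score value and raises week-8 power from about 75%–92% to 86%–96%.

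The power figures rest on assumed values (28 per arm, d = 0.7, rho 0.5–0.7, equal variances). The ratio (1 + rho)/2 depends only on rho and equal variances. The primary HAMD-17 outcome is analysed differently and is not affected, and the abstract classes the EEG outcomes as exploratory. This is a worthwhile improvement to the secondary analyses and no threat to the trial's main conclusion.

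**What to change.** Reword the mixed-model sentence in section 2.14, or settle it in the SAP before unblinding:
- Fit the week-4 and week-8 measurements with arm, visit, arm-by-visit and the baseline value as fixed effects.
- Report active minus sham with a 95% CI at week 4 and at week 8 separately.
- State that this model governs HAMA, MMSE, MoCA, RBANS and the beta/gamma oscillations, and that the general Mann-Whitney sentence does not apply to them.

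The cost is a few sentences. Baseline is already collected, so no extra visit, measurement or participant is needed.

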### Ethics

2.15

The study has received full ethical approval from the Ethics Committee of Xuanwu Hospital, Capital Medical University, Beijing, China (LYS[2018]-092) on September 5, 2018, then amended (LYS[2018]-092-Amendment 1) on May 15, 2019. And the ethics committee's phone, email, and address as follows: [name], [contact], and [name]. The study is registered in the ClinicalTrials.gov (NCT03903068). Participants will provide written informed consent to enroll before the trial and voluntarily withdraw consent or cease to enroll at any time for any reason. The results will be showed at international conferences and published in peer-reviewed journals.

## Discussion

3

Depression is a common complication after stroke and is associated with poor functional outcome and high mortality.^[1,2,4]^ The relation between depression and stroke has been established, and stroke has been shown to elevate the risk of PSD, and conversely, depression is an independent risk factor for stroke.^[4,5,54]^ The most commonly applied antidepressants are SSRI and SNRIs, although having side effects including increased risk of hemorrhagic complications. Because antidepressant agents have the potential to cause a series of adverse effects and are related to poor patient compliance, it is crucial to explore other effective treatments that may have fewer side effects in the management of PSD.

In this trial, we will explore whether the tACS can lessen depression among subjects who have suffered a stroke. Although the efficiency of tACS in improving depression has been proposed as promising evidence,^[49,55–62]^ no evidence with modern rigor methodology has been provided.^[33]^ The therapeutic effect of tACS intervening brain has not been fully understood, it may involve in stimulation sites and neurotransmitter mechanisms.^[63–65]^ This study will be performed as an RCT to provide evidence for the clinical efficacy of the tACS in the treatment of PSD. The outcome of the study will offer evidence-based data regarding whether the tACS is beneficial for participants with PSD. Additionally, brain activities including beta- and gamma-oscillations of PSD participants will be explored in our trial for the possible mechanism of the tACS treating PSD. The results of the trial will be reported at international meetings and published in peer-reviewed journals. Notably, the success of this study will provide a large-scale clinical study to further consolidate the evidence for the use of the tACS in PSD patients.

This trial has some limitations that require consideration. For example, the study is being undertaken in a single center; therefore, it may not necessarily be possible to predict the results from the trial to other regions or ethnic groups. Second, the intervention duration is short.

In conclusion, this prospective trial will present that the tACS can effectively and safely treat PSD, consequently providing a new direction for treating PSD with minimal side effects.

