**Discussion::**

The study will be the first randomized controlled trial to evaluate the efficacy and safety of tACS at a 77.5-Hz frequency and 15-mA current in reducing depressive severity in patients with PSD. The results of the study will present a base for future studies on the tACS in PSD and its possible mechanism.

Trial registration number: NCT03903068, pre-results.

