### Adverse effects

2.7

Adverse events will be recorded on Case Report Forms (CRF) though the overall trial at weeks 4 and 8, according to vital signs, the treatment-emergent symptom scale (TESS) and EEG.

The proportions of participants who have symptoms in the TESS will be analyzed at weeks 4 and 8. TESS is composed of behavioral toxicity, laboratory abnormalities, nervous system, automatic nervous system, cardiovascular system and six other aspects (ranging from 0 to 4, the higher score, the more serious the adverse reactions).

The proportions of participants have an epileptic seizure based on EEG activity and clinical manifestations at weeks 4 and 8.^[52]^ At the request of the local ethics committee, EEG recordings will be monitored for each participant in the neurophysiology lab of the Department of Neurology of Xuanwu Hospital, Capital Medical University according to the electrode locations of the international 10/20 system for EEG recording at baseline and weeks 4 and 8. All participants will be recorded by EEG equipment for more than 30 minutes,^[29]^ and whether the participant will have an epileptic seizure will be assessed by EEG professional technicians and investigators.

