### Randomization and blinding

2.9

An independent statistician, who is not be involved with the enrolment nor the assessment of the study participants, will establish and keep the concealed randomization schedule using a computer-generated random number sequence. The randomization sequence will be computed with the blocks of 4. Participants will be randomized into 2 groups with a ratio of 1:1, and the active and sham groups will be coded A and B, respectively. The code will be set in an opaque envelope and subsequently sealed. 10 tACS devices (5 sham and 5 active) have the same size, color, appearance, weight, and odor, and are coded as A or B. If one participant is allotted to A, only devices coded as A will be used through the course of the intervention, similarly if B, only B devices can be utilized. Two trained nurses of tACS devices will know the tACS devices’ status, but not involved in the assessment of participants and will keep blindness to participants and other study staff about tACS devices. Persons involving in the study, including the investigators, raters, EEG technicians, participants, trial monitors, and statistician, will be blinded to treatment assignment during double-blinded treatment until the end of follow-up.

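### The Discussion promises a safety conclusion that a trial sized only for efficacy, with seizure analysed by logistic regression, cannot support

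*Protocol article*

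**What the plan says.** **Aim.** The Abstract makes safety an aim beside efficacy. Its Discussion paragraph says the study is to "evaluate the efficacy and safety of tACS at a 77.5-Hz frequency and 15-mA current".

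**Announced conclusion.** The last paragraph of section 3 states, before any data exist, that the trial will present that "the tACS can effectively and safely treat PSD, consequently providing a new direction for treating PSD with minimal side effects". The limitations just before it name the single centre and the short intervention. They do not mention how little the sample can show about harm.

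**Sample size.** Section 2.13 sizes the trial by "assuming a 50% improvement rate at the end of 8 weeks in the active group and a 15% in the sham group", with 26 per group for 80% power at two-sided 5%. After attrition, "And the total sample size will be 70". Section 2.9 gives the split: "Participants will be randomized into 2 groups with a ratio of 1:1". No safety outcome enters the calculation.

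**Safety outcomes.** Section 2.7 defines seizure as a proportion of participants at weeks 4 and 8. For the treatment-emergent symptom scale it says: "The proportions of participants who have symptoms in the TESS will be analyzed at weeks 4 and 8".

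**Analysis.** Section 2.14 says that results "will be considered statistically significant at a *P* value < .05, and all tests are two-sided". It gives the chi-square test for categorical variables in general. Its list of variables for logistic regression ends with "CGI-I score, CGI-S score, and epileptic seizure". No margin, tolerable excess or target interval width is attached to any harm.

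**The concern.** A trial can conclude that a treatment is safe only to the extent that its data could have shown otherwise. Here the favourable statement is written in advance and without condition, while the sample was chosen for a large difference in a common efficacy outcome. Uncommon harms are where 35 participants per arm carry least information.

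The method named for seizure adds a technical problem. When one arm has no events, the maximum-likelihood odds ratio is infinite (separation). The standard error of the treatment coefficient becomes enormous and the Wald test cannot reach significance, however many events occur in the other arm. An arm without seizures is a likely result in a trial of this size, so the planned output could be uninformative exactly when a seizure signal matters.

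At stake is what the report says about harm. The Discussion expects success to lead to a large-scale study, so an overstated safety claim would be carried forward.

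**Working it through.** **Inputs from the article.** Total 70, ratio 1:1, hence 70/2 = 35 per arm; 20% attrition, hence 35 × 0.8 = 28 per arm if dropouts give no safety data; two-sided 5% level. The article gives no event rate for any harm, so all harm rates below are assumptions, shown over a range.

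**1. The plan's own figure.** For 50% versus 15%, the mean proportion is 0.325:

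n = [1.960 × √(2 × 0.325 × 0.675) + 0.842 × √(0.50 × 0.50 + 0.15 × 0.85)]² / 0.35² = (1.298 + 0.517)² / 0.1225 = 26.9, so 27 per group.

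The arcsine formula gives 26.1. The stated 26 is reproduced within rounding and choice of formula. At 35 per arm the power for efficacy is about 90%. The efficacy sizing is not in question.

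**2. Logistic regression with no sham seizures.** The estimated log odds in the sham arm is log(0/35), which is minus infinity, so the treatment coefficient has no finite value. Software stops at an arbitrary large number. Fitting 4, 6 and 10 active seizures out of 35 against 0/35 gives a Wald P of about 0.999 each time. At 10/35 the model named in the plan, read by its usual Wald test, would show nothing.

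**3. Chi-square on the same tables.** With k active events against 0/35 (uncorrected):

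χ² = 70 × (35k)² / [35 × 35 × k × (70 − k)]

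- k = 3: 3.13, P = .077
- k = 4: 4.24, P = .039

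So at least 4 of 35 (11%) active seizures are needed. The power for seizure against a true sham rate of 0% is therefore the probability of 4 or more events in 35: 9.6% at a 5% rate and 46.9% at a 10% rate.

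**4. Chi-square power over a range of assumed rates** (exact enumeration of two binomials):

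| Sham vs active | 35 per arm | 28 per arm |
|---|---|---|
| 0% vs 2% | 0.5% | 0.2% |
| 0% vs 5% | 9.6% | 4.9% |
| 0% vs 10% | 47% | 31% |
| 10% vs 20% | 22% | 18% |
| 20% vs 40% | 45% | 38% |
| 10% vs 30% | 56% | 47% |
| 10% vs 40% | 85% | 76% |

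**5. What zero events would exclude.** The upper limit for 0/n is 1 − a^(1/n), with a = 0.05 for a one-sided and 0.025 for a two-sided 95% interval.

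- n = 35: 1 − 0.05^(1/35) = 8.2%; 1 − 0.025^(1/35) = 10.0%
- n = 28: 10.1% and 12.3%

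If the true seizure risk were 2%, the chance of seeing none in 35 active participants would be 0.98^35 = 49%.

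**The case against.** **A stronger reading that the text does not support.** A reader might infer that the trial will treat P > .05 on seizure or TESS as proof of safety. Section 2.14 sets a threshold but never says what a non-significant safety comparison means, and the closing sentence of section 3 is tied to no test. That decision rule is not in the article. Nor can one say that the tests would miss most relevant harms: this depends on the assumed rates, and an excess of 10% versus 40% would be found about 85% of the time at 35 per arm.

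**TESS.** Section 2.7 says only that the proportions will be analysed. A chi-square test follows from the general sentence in 2.14; only seizure is named for the regression.

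**It is only a closing sentence.** Elsewhere section 3 speaks of exploring whether tACS helps and foresees a larger study, so the authors may not regard 70 participants as decisive. That is fair, and it makes this largely a matter of wording. But the sentence is unconditional, and the limitations do not temper it.

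**Reporting detail belongs in a fuller document.** Percentages for categorical variables are already planned, and sizing on efficacy alone is usual. Exact intervals left out of an article would not be a finding by themselves. What stands is that the article does name a method for seizure, and that method fails with an empty arm.

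**Other versions of the test.** The article does not specify Wald. A likelihood-ratio test from the same model would still work: for 4/35 against 0/35 it gives 2 × [4 ln 2 + 31 ln(31/35) − 66 ln(66/70)] = 5.79, P = .016. The odds ratio would nevertheless be infinite and give no usable size of harm, and the chance of seeing enough events would remain low.

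**Attrition.** The 28-per-arm figures assume that dropouts contribute nothing. The plan is intention-to-treat with multiple imputation, so 35 per arm is the main case.

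**Conclusion.** The point holds in this limited form: the article commits in advance to a favourable safety conclusion that its design and its named seizure analysis cannot support. No passage equates non-significance with safety.

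The size at 35 per arm is about 10% chi-square power for 5% versus 0%, 47% for 10% versus 0%, and 22% for a doubling from 10% to 20%. With no sham seizures, the Wald test is uninformative at any active count. A clean record of 0/35 would leave risks up to 10.0% (two-sided 95%) or 8.2% (one-sided) open. The power figures rest on assumed event rates; the zero-event limits and the separation problem do not. The collection of safety data and the efficacy sizing are unaffected.

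**What to change.** **Section 2.14.** Take epileptic seizure out of the logistic-regression list. Report it as counts and proportions per arm, with the risk difference and an exact 95% confidence interval, and report TESS proportions the same way. Where no event occurs, give the upper limit (for 0/35, 10.0% two-sided or 8.2% one-sided). State that a non-significant difference will not be taken as evidence of safety.

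**Section 3.** Make the closing sentence conditional: the trial will estimate efficacy and describe tolerability. Add the limited ability to detect uncommon harms to the limitations.

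**Cost.** Wording in two sections and exact intervals in the safety tables. No extra participants, visits or procedures. The downside is a more modest safety claim.
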